#### Follow-Up procedures

Data will be collected from participants at 6 and 12 months (if applicable) from date of surgery with a target of±1 month, at their routine NHS check-up appointments. If participants do not attend their follow-up appointment, they will be contacted by telephone, and, if appropriate, sent the questionnaires to complete. The study team will attempt to telephone these participants on up to two occasions. If these methods fail, we will categorise the participant as a ‘non-responder’ for that time-point only. The data collection schedule is presented in table 2.

### Outcome measures

Feasibility outcome data to be collected will include:

Screening log numbers of eligible patients, including reasons for exclusion/non-participation.Recruitment numbers and rate; overall and per site.Protocol adherence, including fidelity to control and experimental interventions using treatment logs, timing and location of intervention delivery (in particular the first session) alongside frequency of physiotherapy contact. This will assist in assessing both potential between-group contamination and intervention delivery. We will also monitor the intervention delivery as part of the Quality Assurance monitoring visits. The findings of these visits will provide data on intervention location, fidelity to the protocol, and barriers or facilitators to provision across the sites.Follow-up completion rate and overall study retention in each study arm for the outcome measures highlighted above.

The primary and secondary outcome measures for this trial are presented in table 1.

### Data analysis

#### Sample size

As this is a feasibility study which is not aimed to assess treatment effects, we have not undertaken a formal power sample size calculation.

Sixty participants will be recruited, based on Teare *et al*’s recommendation^30^ that between 50 and 70 are required when continuous scale data outcomes are to be collected. This assumes a 10% drop-out. This will also provide sufficient data to answer our feasibility objectives with 30 participants from each group recruited. Based on 2017 data from two of the participating sites, approximately 160 potentially eligible participants were identified. Based on a conservative judgement of 45% recruitment rate for this rehabilitation trial with this cohort,^19 31 32^ over 60 participants could be recruited within a 12-month period. This is within the required number to conduct this study.

#### Statistical analysis

Recruitment and follow-up rates are the main drivers for the feasibility design on the basis that unless reasonable rates can be achieved no formal trial will be possible. Recruitment rate will be calculated as the number of participants randomised as a proportion of eligible participants. Rates will be estimated based on data collected and a 95% CI determined for these measures. The rate of incomplete information either due to drop-out to the interventions or non-completion of the outcome measures will be based on the number of participants randomised. The statistical analysis will also estimate, with 95% CIs, the parameters required for a formal power calculation, particularly the SD of potential outcome measures.

If the estimated recruitment and follow-up rates are such that a multicentre definitive trial is possible no formal analysis will be undertaken and data from the feasibility will be locked and carried over into the definitive trial, where funding for the definitive trial has been obtained. In this case no formal analysis of treatment efficacy will be undertaken. The definitive trial will be planned based on the data collected during this feasibility study. The mean difference, SD and effect size with between-group inferential statistical analyses will be estimated to determine direction and magnitude of effect and to inform a power calculation for a definitive trial.

The ‘traffic light’ system will be used as a guide for progression to a definitive trial (table 3).^33^ If any of the criteria are not met, these will be discussed by the Trial Steering Committee (TSC) to decide if a definitive trial is feasible.

**Table 3 T3:** Progression criteria for the GRRAND-F trial

	Green (Go)	Amber (Amend)	Red (Stop)
Recruitment	60 participants recruited within 12 months	40–59 participants recruited within 12 months	<40 participants recruited within 12 months
Consent	≥40% of potentially eligible participants	20%–39% of potentially eligible participants	<20% of potentially eligible participants
GRRAND-F intervention fidelity	>70% participants received protocol-compliant GRRAND-F intervention	50%–70% received intervention as randomised	<50% received intervention as randomised
Contamination	<5% participants in control group received GRRAND-F intervention	5%–10% participants in control group received GRRAND-F intervention	>10% participants in control group received GRRAND-F intervention
Data Completion	<15% missing data at 6 months follow-up	15%–30% missing data	>30% missing data
Retention	<20% attrition at 6 months follow-up	20%–50% attrition at 6 months follow-up	>50% attrition at 6 months follow-up

GRRAND-F, Getting Recovery Right After Neck Dissection.

Descriptive statistics will be used to describe the demographics between the two groups. Clinical outcome data will be reported depending on the type of variable: for continuous variables the means and SD in each group (or median and IQR if non-normally distributed) together with the unadjusted and adjusted difference in means and corresponding 95% CIs with analysis of covariance, adjusting for baseline values (where appropriate) and stratification factors; for categorical variables, the number and percentage of participants in each category will be reported and unadjusted and adjusted ORs (for binary outcomes) together with their 95% CIs will be reported.

All results will be based on the intention-to-treat population. Protocol deviations will be reported as these are an important part of the feasibility assessment when planning the definitive trial.

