#### Individualised rehabilitation options

ROM exercises targeting muscles and joints of the face, neck and shoulder impacted by ND. The purpose of these exercises is the prevention of postsurgical contracture, and the maintenance of swallowing and upper limb mobility.Progressive resistance exercises, targeting strengthening of the neck and shoulder. Resistance loads will initially be set at a moderate level of exertion (based on the modified Borg scale of perceived exertion^20^) to permit progression, enhance motivation and adherence, and reduce the possibility of symptom flare-up. Resistance will consist resistance bands at the shoulder and isometric resistance provided by the participant’s hand for neck and temporomandibular joint exercises.

Exercises will be progressed by increasing the resistance load, speed, number of repetitions and sets or by progressing the range in which the exercise is completed and through the introduction of weight-bearing exercises through the upper limb. Additionally, the exercises will become increasingly ‘task specific’, targeting participant’s specific functional goals.

Education and advice on a number of recognised potential postoperative complications including:Positioning limbs to prevent joint contractures.Oral health particularly for patients following upper cervical/head/oral surgery.Pain management for both early and later postoperative stages through positioning, taking prescribed analgesics and pacing/behaviour modfication.Scar management.Exercise adherence and return to function with fatigue management and pacing of activities.Promote independence and confidence to return to normal activities of daily living, work and social pursuits.

This will be delivered through the introduction of techniques of goal setting, fear avoidance, pacing and fatigue management, behaviour modification and graded activity. This has been successfully taught and delivered by the research team in previous National Institute for Health Research trials (BOOST,^21^ DAPA^22^), to provide a basis for this new intervention. Advice will be provided through discussion during consultations and re-enforced with worksheets designed by the multidisciplinary trial team.

The intervention may be modified in the development phase of the trial. The intervention will be finalised prior to the main trial. If there are no substantive changes, participants will contribute to the main trial analysis.

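### The plan promises no efficacy analysis before carry-over into the definitive trial, yet also an unconditional between-group analysis to size that trial; both cannot be followed

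*Protocol article*

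**What the plan says.** All of the main text is in the Protocol article under Data analysis, Statistical analysis.

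- **Carry-over branch.** If recruitment and follow-up rates make a multicentre definitive trial possible, "no formal analysis will be undertaken and data from the feasibility will be locked and carried over into the definitive trial", subject to the condition "where funding for the definitive trial has been obtained". The next sentence reinforces it: "In this case no formal analysis of treatment efficacy will be undertaken".
- **Between-group analysis.** Two sentences further on in the same paragraph: "The mean difference, SD and effect size with between-group inferential statistical analyses will be estimated to determine direction and magnitude of effect". Its stated use is "to inform a power calculation for a definitive trial". No condition is attached.
- **Second statement of it.** After Table 3, continuous clinical outcomes are to be reported by group "together with the unadjusted and adjusted difference in means and corresponding 95% CIs with analysis of covariance", with odds ratios for binary outcomes. Again there is no condition.
- **Related text.** The Sample size section opens "As this is a feasibility study which is not aimed to assess treatment effects" when explaining why there is no power calculation. The section on individualised rehabilitation options adds: "If there are no substantive changes, participants will contribute to the main trial analysis".

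No adjustment for an unblinded look at the data is mentioned.

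**The concern.** An analyst cannot both refrain from an efficacy analysis before locking the data and estimate the direction and magnitude of effect in order to power the next trial. The order of events makes a collision likely. A power calculation normally precedes a funding award, whereas carry-over depends on that award. The effect could therefore be examined before the data are declared locked and unanalysed.

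What is at stake is whether these 60 participants can validly count in the definitive analysis. When an observed effect sets a trial's final size, a large early estimate leads to a small trial in which that estimate keeps a large weight. A small early estimate leads to a large trial in which it is diluted. Pooling without adjustment then overstates a true benefit and raises the type I error. Even without pooling, an effect estimated from so few participants is a weak basis for a sample size.

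**Working it through.** **1. The plan's own figures.** From the Sample size section: about 160 potentially eligible, 45% recruitment, 60 recruited (30 per group), 10% drop-out, recommended range 50 to 70.
- 160 × 0.45 = 72, which is over 60, as stated.
- 60 × 0.90 = 54 evaluable, inside 50 to 70. With 1:1 allocation that is 27 per arm.

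The plan states no alpha, power or effect size, so everything below that uses them is an assumption.

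**2. Precision of the observed effect** (in SD units).
- SE = sqrt(2/27) = 0.272.
- 95% half-width = 1.96 × 0.272 = 0.53 SD.
- If the true effect is 0.3 SD (assumed), the chance of the wrong sign is Φ(-0.3/0.272) = 13.5%. The chance of observing more than 0.5 SD is 1 - Φ(0.2/0.272) = 23.1%.

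**3. What that does to sizing.** Assume two-sided 5% and 90% power, so n per arm = 2 × (1.960 + 1.282)² / d² = 21.01/d².
- d = 0.3: 21.01/0.09 = 233.5, so 234 per arm.
- One SE too high, d = 0.572: 21.01/0.327 = 64.2, so 65 per arm.
- One SE too low, d = 0.028: 21.01/0.00078, more than 26,000 per arm.

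**4. Doing both: size on the observed effect, then pool.** Simulation, 1,000,000 runs per setting. Stage 1 has 27 per arm. The total per arm comes from the formula above, using the observed effect and SD, with a floor of 54 and a cap. The final test is an unadjusted z-test on all data. No rule on whether to proceed is imposed.

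| Cap per arm | Two-sided type I error | Overstatement at true 0.3 SD |
|---|---|---|
| 200 | 6.3% | 0.029 SD |
| 400 | 6.6% | 0.036 SD |
| 1000 | 6.8% | 0.039 SD |

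The one-sided error is 3.1-3.4% against 2.5%. A second set of limits (at least 30 new participants per arm, cap 300) gives 6.4% and 0.032 SD. Varying the minimum from 10 to 100 new participants and the cap from 150 to 600 gives 5.7-6.8% and 0.014-0.043 SD.

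**5. Comparators** (at least 30 new per arm, cap 300).
- Pool, but size on the SD only with a fixed target difference (0.4 SD assumed): two-sided error 5.0%, bias about 0.000 SD.
- Size on the observed effect, but analyse new participants only: 5.0%, bias about 0.000 SD.

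So the distortion comes from using the observed effect together with unadjusted pooling. Removing either one removes it.

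**The case against.** The strongest defence is a two-branch reading: the between-arm analysis applies only when the data are not carried over, for instance if funding fails. That is possible, but the text does not say it, and the stated purpose of the analysis is to power the definitive trial, which is the situation in which carry-over is foreseen. It is also fair that the section singles out the SD as the parameter of main interest, and sizing on the SD alone is harmless. That limits the bias to the case where the observed effect is actually used; it does not reconcile the sentences.

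A reader might infer more than the document supports:

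- **That the effect decides whether to proceed.** If the trial went ahead only on a favourable observed direction, the one-sided error among trials that proceed would be about 5.4-5.5%. But no text sets such a rule. Recruitment and follow-up are named as the main drivers, and none of the six criteria in Table 3 concerns efficacy. Without that rule the figure is 3.1-3.4%.
- **That a definitive trial sized one SE too high has 40% power.** That holds for 65 per arm made up entirely of new participants, at a true 0.3 SD. With carry-over, 27 per arm have already been observed at 0.572 SD and 38 are new, so the chance of a significant pooled result is about 70%, itself inflated by the reuse.
- **That the judgement on substantive changes to the intervention would be made with outcomes known.** The intervention section refers to modification in a development phase and gives no timing relative to outcome analysis. Its main trial may also mean the randomised phase of this study. The point does not need that sentence.
- **That the Sample size section forbids between-arm estimates.** Its remark on aims explains the absence of a power calculation. Reporting estimates with intervals does not by itself contradict it.

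Finally, the feasibility objectives are unaffected, and the definitive trial could still exclude or adjust for these data. That bears on how much harm follows, not on whether the text is consistent.

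**Conclusion.** The contradiction stands on the text: the no-analysis commitment and the unconditional between-group commitments cannot both be honoured, and a separate analysis plan could honour only one of them. The statistical consequence is real but modest, and conditional on the observed effect setting the definitive sample size and on pooling without adjustment. It then amounts to a two-sided type I error of about 6.3-6.8% instead of 5%, and an overstatement of about 0.03-0.04 SD at a true 0.3 SD. The 5% alpha, 90% power, true effect and caps are assumptions; the 27 per arm follows from the plan's own figures. The poor precision of the observed effect is a separate weakness that holds with or without carry-over.

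**What to change.** State two mutually exclusive branches in the paragraph on carry-over, and make the paragraph after Table 3 follow them.

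1. **If the data may be carried over:** before lock, estimate only the feasibility rates and the pooled (blinded) SD with its 95% CI. Apply Table 3 without sight of clinical outcomes by arm. Take the target difference for the definitive trial from outside these data. Blinding the progression decision matters even with SD-only sizing, because proceeding only on a favourable direction would still give a one-sided error of about 4.4% after pooling (cap 300, target 0.4 SD, both assumed).
2. **If the between-arm estimates are produced:** label them descriptive, and either leave these participants out of the definitive analysis or pre-specify a method, such as a combination test, that controls type I error.

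This is a change of wording only, but it must be made before any by-arm look, which cannot be undone. The cost is that the feasibility report has no between-arm clinical estimates if the data are carried over. Under the second branch, the definitive analysis loses the feasibility data unless the pre-specified method is used.

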**Secondary objectives**		
To determine potential risks of intervention contamination.	Intervention logs and qualitative interviews (face to face with patients/telephone based with physiotherapists).	Completion of intervention and qualitative interviews.
To determine feasibility and acceptability of the intervention from patient and physiotherapist perspectives.	Intervention log, cross-over event as reported in protocol deviation forms, attrition rate and ‘did not attend’ rates for intervention. Qualitative interviews. Safety reporting forms.	Completion of intervention and qualitative interviews.
To estimate the sample size calculation for a definitive trial.	Expected primary and secondary outcome measure: Shoulder Pain and Disability Index (overall and pain and function sub-scales); EQ-5D-5L; EORTC quality of life questionnaire (C30 core and disease-specific H&N43); health resource use questionnaire; adverse events; shoulder/neck range of motion and grip strength.	At the end of the trial.
To determine wider experiences and perceptions of the study design from a patient and physiotherapist perspective.	Qualitative interviews.	Completion of the qualitative interviews.

EORTC, European Organisation for Research and Treatment of Cancer; GRRAND-F, Getting Recovery Right After Neck Dissection; H&N43, Head and Neck 43 Questionnaire.

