### Randomisation, blinding and allocation concealment

Following the completion of the consent process baseline data will be collected. Participants will then be randomised once their eligibility has been confirmed post-operatively prior to hospital discharge.

Participants will be randomised in a 1:1 ratio using the centralised web-based randomisation service provided by Oxford Clinical Trials Research Unit. Randomisation will be undertaken using minimisation to ensure balanced allocation of participants across the two treatment groups, stratified by hospital site and spinal accessory nerve sacrifice.

The minimisation algorithm will incorporate a non-deterministic element and will be seeded using simple randomisation to prevent predictability in the early stages of the study.

Due to the nature of the intervention, participants and clinicians delivering physiotherapy will not be blinded to treatment allocation.

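### The observed between-group effect from about 54 evaluable participants should not inform the definitive trial's power calculation, and the plan contradicts itself on whether it is estimated at all

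*Protocol article*

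**What the plan says.** All references are to the protocol article.

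- **Sample size.** The study is described as a "feasibility study which is not aimed to assess treatment effects", and for that reason no formal power calculation was made. "Sixty participants will be recruited", "with 30 participants from each group recruited", on a rule of thumb of 50 to 70 for continuous outcomes. "This assumes a 10% drop-out".
- **Statistical analysis, first paragraph.** The parameters needed for a power calculation will be estimated with 95% CIs, and the SD is singled out among them.
- **Statistical analysis, second paragraph.** If a definitive trial proves possible, the data are locked and carried over (given funding), and in that case there is to be no formal efficacy analysis. The definitive trial will be planned on the data from this study. The paragraph's last sentence covers the SD and the difference in means as well, and goes on: "effect size with between-group inferential statistical analyses will be estimated to determine direction and magnitude of effect and to inform a power calculation".
- **Statistical analysis, after Table 3.** Unadjusted and covariance-adjusted differences with 95% CIs are planned for continuous outcomes.
- **Table 1, secondary objectives.** Sizing the definitive trial is a listed objective. Its outcomes are given as "Expected primary and secondary outcome measure: Shoulder Pain and Disability Index", followed by the quality-of-life, resource-use, adverse-event and physical measures. The list does not say which is primary.

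The article names no minimum important difference or other external target.

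**The concern.** An SD can be estimated usefully from about 54 people. A between-group difference cannot be estimated closely enough to serve as a planning target. Required sample size varies with the inverse square of the target difference, so an error in that difference is magnified in the size of the next trial. A chance-high estimate gives an underpowered trial. A chance-low one gives a trial far larger than needed.

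The text also pulls in different directions. One section disclaims any aim of assessing treatment effects. Another assigns to inferential between-group analyses the task of establishing the direction and size of the effect. Within one paragraph, efficacy analysis is excluded if data are carried over, and the between-group analysis is then planned with no condition attached.

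**Working it through.** **The plan's own figures.** No alpha, power or effect size is stated, so there is no power formula to reproduce. The counts agree: 60 × (1 − 0.10) = 54 evaluable, and 54 / 0.90 = 60, which lies within 50 to 70. Allocation is 1:1 ("Participants will be randomised in a 1:1 ratio using the centralised web-based randomisation service"), so there are 27 per arm.

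**Precision of a standardised difference.**
- Unadjusted: SE = √(2/27) = 0.272 SD. Half-width = t(0.975, 52 df) × 0.272 = 0.55 SD.
- Covariance-adjusted, assumed baseline correlation r = 0.6: SE = 0.272 × √(1 − 0.36) = 0.218. Half-width = 0.44 SD.
- At the edge of the green retention band in Table 3 ("<20% attrition at 6 months follow-up"), about 48 are evaluable, 24 per arm: SE = √(2/24) = 0.289. Half-width = 0.58 SD unadjusted.

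**Assumptions not in the documents.** True effect d of 0.2, 0.3, 0.5 or 0.8 SD; definitive trial at 90% power and two-sided 5%; SD treated as known; the observed positive effect used directly as the target difference.

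**Formulas.**
- Wrong sign: Φ(−d/SE).
- 95% CI includes zero: 1 − [Φ(d/SE − 1.96) + Φ(−d/SE − 1.96)].
- Definitive n per arm from an observed effect d̂: 2 × (1.960 + 1.282)² / d̂².
- True power at that n is below 80% when d̂ exceeds d × (1.960 + 1.282)/(1.960 + 0.842) = 1.157 d. The last column is P(d̂ > 1.157 d) / P(d̂ > 0), by simulation with n rounded up.

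**Unadjusted results, 27 per arm.**

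| True d | Correct n per arm | Wrong sign | CI includes zero | True power < 80%, given d̂ > 0 |
|---|---|---|---|---|
| 0.2 | 526 | 23% | 89% | 59% |
| 0.3 | 234 | 13.5% | 80% | 50% |
| 0.5 | 85 | 3.3% | 55% | 40% |
| 0.8 | 33 | 0.2% | 16% | 31% |

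Without rounding n up, the last entry is 32%.

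With the observed effect covariance-adjusted at r = 0.6 and the definitive trial sized by the same formula, the CI includes zero in 85%, 72%, 37% and 4%. True power is below 80% in 54%, 45%, 36% and 28%.

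**Worked case, d = 0.3.** The middle half of observed effects runs from 0.3 − 0.674 × 0.272 = 0.12 to 0.3 + 0.674 × 0.272 = 0.48. The planned n per arm then runs from 1,551 down to 90, against a correct 234. With 90 per arm, true power is Φ(0.3/√(2/90) − 1.96) = 52%.

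**If only the SD is taken from this study.** With 52 df its 95% CI is 0.84 to 1.24 times the estimate. For a fixed target difference the required n then varies by a factor of 0.70 to 1.53.

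**The case against.** The strongest reply is that the text says the effect will help inform a power calculation, alongside an SD to which the section gives more weight. Nothing says that the point estimate will be entered as the target difference. That is fair. A reader might infer that the observed effect is the sole basis for sizing, but the wording does not go that far, so the power figures above show what follows if it is used that way. They are not a forecast. The reply does not remove the point, because the article offers no other target and gives determining the effect as a stated purpose of the analysis.

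A second reply is that the planned covariance adjustment improves precision. It does, from ±0.55 to about ±0.44 SD at r = 0.6, which is still wide.

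A third is that the important difference can be set in the definitive trial's own protocol. This also stands: its absence here is no error in itself. The fault lies in what the present text plans to use in its place.

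Three stronger readings are tempting but unsupported:
- That the primary outcome will be chosen because it shows the largest effect. Table 1 leaves the choice open, which is normal at this stage, and lists the shoulder index first. No rule selects by observed effect.
- That a reversed estimate would stop the programme. Table 3 contains no efficacy criterion.
- That the study was sized only to estimate an SD. The Sample size section refers to continuous outcomes and the feasibility objectives, and does not say that.

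**Conclusion.** The point holds as a fault in a stated rule and as a contradiction between and within sections. The 95% CI of about ±0.55 SD unadjusted (±0.44 SD adjusted at r = 0.6) is too wide for the observed effect to set or steer a target difference. If it were used that way, mis-sizing would be likely but not inevitable.

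A reader might go further and say that the study cannot show even the direction of effect. That depends on the true effect. The point estimate has the right sign in about 77% of studies at 0.2 SD and 97% at 0.5 SD, and direction would be clear near 0.8 SD. For small to moderate effects the interval will more often than not include zero, except at 0.5 SD after adjustment (37%).

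A reader might also say that the definitive trial would be mis-sized whether or not data are carried over. The text does not settle this, because it excludes efficacy analysis in the carry-over case and then plans a between-group analysis without condition.

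The true effects, the baseline correlation and the definitive trial's alpha and power are assumptions; the documents give none of them.

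**What to change.** Reconcile the Sample size and Statistical analysis sections. In the last sentence of the second Statistical analysis paragraph, remove the between-group inferential testing and the stated purpose of establishing direction and magnitude. Replace it with wording such as:

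> The definitive trial will be powered on a pre-named minimum important difference in a pre-named primary outcome. This study will supply only the SD with its 95% CI, the baseline to follow-up correlation, and the recruitment and attrition rates. Between-group differences will be reported descriptively with confidence intervals and will not be used to set the target difference.

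State also whether this descriptive reporting applies when data are carried over, so that it agrees with the exclusion of formal efficacy analysis in that case.

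The cost is a change of wording. No new data are needed, and the SD and rates are already planned. Planning on an upper limit of the SD is optional. At the one-sided 80% limit the factor is 1.096, and 1.096² = 1.20, so the definitive sample would be about 20% larger.
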